## Abstract

**Background:**

Impaired cervical joint position sense and balance are associated with neck pain. Specific therapeutic exercise and manual therapy are effective for improving neck pain and functional ability but their effects on joint position sense and balance impairments remain uncertain. Changes in the joint position sense and balance may need to be addressed specifically. The primary objective is to investigate the most effective interventions to improve impaired cervical joint position sense and balance in individuals with neck pain. The secondary objective is to assess the effectiveness of the interventions on pain intensity and disability, pain location, dizziness symptoms, cervical range of motion, gait speed, functional ability, treatment satisfaction and quality of life.

**Methods:**

A 2 × 2 factorial, single blind RCT with immediate, short- and long-term follow-ups. One hundred and sixty eight participants with neck pain with impaired joint position sense and balance will be recruited into the trial. Participants will be randomly allocated to one of four intervention groups: i) local neck treatment, ii) local treatment plus tailored sensorimotor exercises, iii) local treatment plus balance exercises, and iv) local treatment plus sensorimotor and balance exercises. Participants receive two treatments for 6 weeks. Primary outcomes are postural sway and cervical joint position error. Secondary outcomes include gait speed, dizziness intensity, neck pain intensity, neck disability, pain extent and location, cervical range of motion, functional ability, perceived benefit, and quality of life. Assessment will be measured at baseline, immediately after treatment and at 3, 6, 12 month-follow ups.

**Discussion:**

Neck pain is one of the major causes of disability. Effective treatment must address not only the symptoms but the dysfunctions associated with neck pain. This trial will evaluate the effectiveness of interventions for individuals with neck pain with impaired cervical joint position sense and balance. This trial will impact on clinical practice by providing evidence towards optimal and efficient management.

**Trial registration:**

ClinicalTrials.gov (NCT03149302). May 10, 2017.

## Background

Neck pain is a common musculoskeletal disorder and a costly public health issue [1, 2]. The pain is often persistent or recurrent in nature [3, 4]. The underlying mechanisms for recurrence or persistence remain unclear but could be associated with altered proprioception from the neck muscles, which have a vital and unique role in providing input for cervical joint position sense, head and eye movement control and postural stability [5–7]. Patients with neck pain not uncommonly experience symptoms of dizziness/light headedness and unsteadiness [8, 9]. Such patients usually have impaired proprioception (cervical joint position sense) and postural instability which account for these symptoms [10–13]. These impairments can lead to decreased physical performance and increased concerns of falling, particularly the elderly [14, 15]. Further, dizziness and unsteadiness have been shown to be predictors of both poorer recovery [16] and poorer response to musculoskeletal treatment [17–19]. Thus it is important to address such symptoms and disturbances in patients with neck pain not only to gain symptomatic relief but also to reverse the impairments to improve physical performance and function.

Evidence suggests that conventional treatment of manual therapy and specific therapeutic exercise directed towards neuromuscular impairments are effective interventions for relieving neck pain [20, 21] and dizziness symptoms [22, 23] and they improve cervical joint mobility and neck muscle performance [24–26]. However, these interventions are not specifically directed towards impaired cervical proprioception and balance. The effects of exercise and manual therapy on proprioception (joint reposition sense) and balance remain uncertain [23, 24, 27].

It is recommended that changes in cervical joint position sense and balance are addressed to optimize outcomes [23, 28]. There is preliminary evidence to suggest that sensorimotor training can improve impaired cervical joint position sense [29–32], but it is unknown if sensorimotor training can improve balance or indeed if balance training can resolve impairments in cervical joint position sense. Is one, both or neither training required in addition to conventional treatment to treat patients with neck pain and proprioceptive and balance disturbances? This is an important question as it is necessary to not only understand treatment effects but also to develop the most efficient treatment strategies.

This is a mechanistic randomized clinical trial in which the effects of treatment on measures of balance and cervical proprioception will be examined. This trial will evaluate the short- and long-term benefits of conventional local treatment to the neck with and without additional sensorimotor control and balance exercise approaches for people with chronic neck pain. The primary objective is to investigate the most effective and efficient interventions to improve disturbances in cervical joint position sense and balance. More specifically, we will test if local treatment to the neck (manual therapy and therapeutic exercise) is sufficient, or whether the addition of sensorimotor control and balance exercise has a superior effect. As it is unclear whether sensorimotor control exercises will automatically improve balance and vice versa, we will also test their effects separately as well as collectively. To achieve our objective, we will test four treatment groups: (i) local neck treatment alone, (ii) local treatment plus tailored sensorimotor control exercises (joint position sense and oculomotor control), (iii) local treatment plus balance exercises and (iv) local treatment plus both sensorimotor control and balance exercises. The secondary objective is to assess the effectiveness of the interventions on neck pain intensity, neck disability, pain extent and location, any dizziness symptoms, cervical range of motion, gait speed, functional ability, treatment satisfaction and quality of life.

### Study hypotheses

Primary hypothesis: Specific training of impairments in sensorimotor control and balance will be superior for improving impairments in neck proprioception and balance.

Secondary hypothesis: Specific training of impairments in sensorimotor control and balance will be superior for reducing dizziness intensity and increasing gait speed. There will be no differences between intervention groups in outcomes of neck pain intensity, neck disability, pain extent and location, cervical range of motion, functional ability, treatment satisfaction and quality of life.

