### Sample size

The sample size estimates are calculated based on the primary outcomes (postural stability and cervical JPE) from baseline to follow-ups. According to our previous data, we consider a sample size that gives 80% power with a 5% confidence level to detect a significant difference of 21.9 cm^2^ (SD = 12.3) for postural sway and 4.5° (SD = 3.2) for JPE. Sample size estimates were performed using both two-way ANOVA and repeated measure ANOVA (two-tailed) and the optimum number of 35 participants per group is required. To allow for 20% drop out rate, a total sample size of 168 participants (42 per group) will be recruited for this trial.

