### Statistical analysis

SPSS version 17.0 or higher will be used for statistical analysis. Descriptive statistics will be used to describe demographic data and baseline characteristics and follow-ups for each treatment group. Two-way mixed ANOVA will be used to determine within-subject and between subject variables. Main effects for independent variables (local treatment/sensorimotor exercise and local treatment/balance exercise) and the intervention effects of the independent variables immediately after treatment and at 3, 6 and 12 month follow-ups will be analyzed. This allows the individual effects of sensorimotor exercise and balance exercise to be examined as well as whether there will be an additive effect of applying both sensorimotor and balance exercises in a multimodal treatment. Differences in mean change (baseline minus follow-up) will be compared between groups using baseline values of the outcomes as covariates.

Effect sizes will be calculated by taking the difference in mean changes in the primary outcomes between the intervention groups and control group (local neck treatment alone). An effect size of 0.2 will be regarded as small, 0.5 as medium and 0.8 as large [55]. Main comparative analysis for primary and secondary outcomes will be performed using an intention-to-treat approach. To address missing data, multiple imputation will be performed as a sensitivity analysis. The significance level will be set at 0.05.

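### The no-difference hypothesis on seven secondary outcomes is paired only with difference tests, which can reject it but cannot support it

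*Protocol article*

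**What the plan says.** The Study hypotheses section splits the secondary hypothesis in two. For dizziness intensity and gait speed it predicts superiority of the specific training. For the remaining secondary outcomes it predicts the opposite kind of result: "There will be no differences between intervention groups in outcomes of neck pain intensity, neck disability, pain extent and location", continuing with "cervical range of motion, functional ability, treatment satisfaction and quality of life". Counting pain extent and location as one, that makes seven outcomes.

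The Statistical analysis section makes no such split. It says "Two-way mixed ANOVA will be used to determine within-subject and between subject variables", names main effects of the two added exercise components at each follow-up, and continues: "Differences in mean change (baseline minus follow-up) will be compared between groups using baseline values of the outcomes as covariates". It extends this to all outcomes ("Main comparative analysis for primary and secondary outcomes will be performed using an intention-to-treat approach") and closes with "The significance level will be set at 0.05".

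No margin, equivalence or non-inferiority test, or confidence-interval criterion is given for the seven outcomes. The Sample size section rests on postural sway and joint position error alone. The standardised effect sizes described under Statistical analysis are likewise limited to the primary outcomes.

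**The concern.** A hypothesis that groups do not differ is an equivalence statement. A test of difference takes that statement as its null, so it can produce evidence against it but none for it. Under the analysis as written, the only outcome compatible with the hypothesis is p > 0.05. That result becomes more likely as measurement gets noisier or more participants are lost, so poor data would favour the hypothesis.

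At stake is what the report can say about pain and disability, which matter to patients and clinicians. The Discussion expects the findings to feed into practice guidelines. A statement that the added exercises leave pain and disability unchanged should not be reachable through imprecision.

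**Working it through.** **Plan's own figures.** The article gives no power or precision figure for the seven outcomes, so there is none to reproduce. Its sample-size figures are 35 analysed per group and 35 × 1.2 = 42 recruited per group, and 42 × 4 = 168. The 35 does not follow from a simple two-group comparison with the stated differences and SDs (two-sided 0.05, 80% power):
- sway: 2 × (1.96 + 0.84)² / (21.9/12.3)² ≈ 5 per group
- joint position error: 2 × (1.96 + 0.84)² / (4.5/3.2)² ≈ 8 per group

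That is a separate matter. Here 35 per group is taken as given.

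**Inputs.** n = 35 analysed per arm and 1:1:1:1 allocation, so a factorial main effect compares 70 with 70. Alpha is 0.05, taken as two-sided because the Sample size section describes its tests as two-tailed. True differences d are in SD units. The article gives no SD for these outcomes, so 0.3 and 0.5 SD are illustrative. (Its own scale calls 0.5 medium, but offers that for the primary outcomes and not as a margin.) Outcomes are treated as roughly normal, without credit for baseline adjustment.

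**Standard errors (SD units).**
- Main effect: √(2/70) = 0.169
- Arm against arm: √(2/35) = 0.239

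**Chance of non-significance when a true difference exists.** P = Φ(1.96 − d/SE).

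| True difference | Main effect, 70 v 70 | Arm v arm, 35 v 35 |
|---|---|---|
| 0.3 SD | Φ(1.96 − 1.775) = 57% | Φ(1.96 − 1.255) = 76% |
| 0.5 SD | Φ(1.96 − 2.958) = 16% | Φ(1.96 − 2.092) = 45% |

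The noncentral t distribution gives 58% and 16% for main effects, and 76% and 46% for arms.

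**Precision.** The 95% CI half-width for a main effect is 1.96 × 0.169 = 0.33 SD. It is 0.30 SD with no loss (84 v 84). On the pain VAS:
- assumed SD 20 mm: 1.96 × 20 × 0.169 = ±6.6 mm
- assumed SD 15 to 25 mm: ±5.0 to ±8.3 mm

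Baseline adjustment would narrow this. With an assumed baseline correlation of 0.5, 6.6 × √(1 − 0.25) ≈ ±5.7 mm.

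**What an equivalence test could deliver.** For two one-sided tests (TOST) at 0.05, equivalent to a 90% CI lying inside ±m, with a true difference of zero, power = 2Φ(m/SE − 1.645) − 1. For main effects:
- m = 0.5 SD: 2Φ(2.958 − 1.645) − 1 = 81%
- m = 0.3 SD: 2Φ(1.775 − 1.645) − 1 = 10%

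If the whole 95% CI must lie inside the margin, 1.96 replaces 1.645. The figures become about 68% at 0.5 SD and effectively zero at 0.3 SD. For 80% TOST power, a 0.3 SD margin needs 2 × ((1.645 + 1.282)/0.3)² ≈ 191 on each side of the comparison, against 70 available.

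**The case against.** The strongest reply is that the sentence is only an expectation: the added exercises should act on their targets and not elsewhere. The stated secondary objective is to assess effectiveness on these outcomes, and a difference analysis suits that. How null secondary results are interpreted is often left to an analysis plan that is not shown here.

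Part of this stands. A reader might infer that the plan has adopted a rule that p > 0.05 proves no difference. The article says no such thing, and that reading is not supported. What remains is a mismatch between two things the article itself fixes: a hypothesis listed alongside the superiority claims, and an analysis that cannot bear on it in the direction claimed. If only an expectation is meant, saying so resolves the point.

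Two further readings go too far. A reader might tie the no-difference claim to the question of which treatment is most efficient, but the Background attaches efficiency to joint position sense and balance, the primary objective, and not to pain or disability. A reader might also take the arm-against-arm figures as the plan's main precision. The analysis section names factorial main effects, for which the chance of missing 0.5 SD is 16% and not 45%. The arm-level figures still have some relevance, since the hypothesis speaks of the intervention groups.

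The outcomes are secondary, and neither the primary hypothesis nor the sample-size basis depends on this sentence.

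**Conclusion.** The concern holds as a mismatch between hypothesis and analysis, of moderate weight. A non-significant main effect would still leave differences of around a third of an SD open, and a true 0.3 SD effect would go undetected more often than not. These sizes assume 35 analysed per arm, a two-sided 0.05 level, no interaction between the two components when main effects are read, and no gain from baseline adjustment. The millimetre values rest wholly on an assumed VAS SD. The logical point depends on none of these assumptions: without a margin or interval rule, no result of the stated analysis can support the hypothesis.

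**What to change.** Reword the second part of the secondary hypothesis, for example:

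> We do not expect the groups to differ on these outcomes. Effects will be estimated with 95% confidence intervals, and a non-significant result will not be read as evidence of no difference.

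This needs no change to design, sample size or data collection. The cost is that many of these outcomes will be reported as inconclusive.

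If an equivalence claim is wanted for neck pain VAS or NDI, prespecify a justified margin for each and judge the 90% CI (TOST) of each main effect against it. At the planned size that is realistic only for a margin near 0.5 SD, and whether so wide a margin can be justified must be argued first. For most of the seven outcomes, rewording is the practical choice.

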## Methods/design

### Trial design

The trial utilizes a single blind 2 × 2 factorial design, and conforms to the CONSORT recommendations [33].

### Participants

A sample of 168 women and men aged 18 years and older with neck pain and JPS and balance impairments will be recruited from the communities in Chiang Mai province, Thailand by advertising through community centers, radio, and Facebook, placing posters in hospitals, physiotherapy clinics and universities, and using our database of participants with neck pain who participated in previous studies and have given consent for future contact. Participants who respond to the advertisements will be screened by a research assistant via telephone interview. They will be potentially eligible for the trial if they meet the eligibility criteria (Table 1).

**Table 1 Tab1:** Inclusion and exclusion criteria

*Inclusion criteria*
- Aged ≥18 years
- Insidious neck pain for at least 3 months
- Average neck pain intensity over the past week ≥30 mm (100 mm visual analogue scale)
- Score ≥ 10/100 on the Neck Disability Index-Thai version (NDI-TH) [47]
*Exclusion criteria*
- Previous history of neck and head trauma or surgery
- Known or suspected vestibular pathology, vertigo or dizziness from ear or brain disorders, sensory nerve pathways (e.g. BPPV), or vascular disorders (e.g. migraine, hypertension)
- Any musculoskeletal or neurological conditions that could affect balance
- Inflammatory joint disease
- Systemic conditions
- Cognitive impairment
- Taking four or more medications
- Received physiotherapy treatment for their neck disorder in the past 12 months

For those provisionally eligible for the trial, appointments will be made with an experienced physiotherapist who will be blinded to participant group allocation if accepted for the trial. The experienced physiotherapist will perform a physical examination of the neck and test sensorimotor function and balance. The physical examination includes:*Tests of cervical joint position error (JPE)* [9, 13]*.* The task is to return to the starting position as accurately as possible with the blindfold. Three trials will be performed of right and left rotation and extension. An average absolute error of > 4.5° in any direction is indicative of a deficit in cervical joint position sense [34].*Tandem stand test* [35]. The participants stand heel to toe with the dominant foot behind the non-dominant foot on a firm surface with eyes closed (age ≤ 45 years) or with eyes open (age > 45 years) [36]. An inability to maintain the standing position without taking a step for 30 s indicates balance impairment [36].*Manual examination of the cervical spine.* The physiotherapist will palpate the cervical facet joints from C0-1 to C7-T1 bilaterally. A joint will be classified as symptomatic by a combination of pain provoked > 2/10 and the physiotherapist’s rating of at least moderately abnormal tissue resistance [37].

All participants will be provided information about the study and enrolled into the trial if they meet all eligibility criteria and voluntarily sign an informed consent statement.

### Procedure

Eligible participants who have agreed to participate in the study will be randomly allocated to one of four treatment groups; local neck treatment (cervical mobilization and therapeutic exercise), local neck treatment combined with sensorimotor control exercises, local neck treatment combined with balance exercises, or local neck treatment combined with sensorimotor control and balance exercises. Interventions will be provided in 12 physiotherapy sessions over a 6-week intervention period (2 visits per week) [26]. Baseline and follow-up assessments (post-treatment and 3, 6 and 12 months) will be conducted at the Department of Physical Therapy, Chiang Mai University by an assessor who is blinded to treatment allocation. The participants will be requested to refrain from seeking other forms of treatment during the trial. Medication for pain may be taken, if necessary, but the participants will be asked to record the type and dose of medication in a medication diary. The flow chart of the trial is presented in Fig. 1.

**Fig. 1 Fig1:**
[figure not shown]
Flow diagram of the trial protocol

### Physiotherapist training and treatment fidelity

The interventions will be provided by five physiotherapists who are experienced in the trial interventions and who have at least 5 years clinical experience in musculoskeletal physiotherapy. Each physiotherapist will deliver all intervention arms. The physiotherapists will attend a 3 h training session to enhance standardization of the interventions. The physiotherapists will be randomly assigned to each participant using computerized random numbers. Training will be provided by an experienced musculoskeletal physiotherapist and trial physiotherapists will receive a detailed procedural and treatment manual. Participant case notes will be monitored as will be selected. Treatment sessions will be audited to ensure that the physiotherapists are managing patients as per the trial treatment protocols.

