### Randomization and allocation concealment

All eligible participants will be randomly allocated to one of four intervention groups: i) local neck treatment, ii) local treatment plus sensorimotor control exercises, iii) local treatment plus balance exercises, or iv) local treatment plus sensorimotor control and balance exercises. Randomization will be undertaken by an independent person with no other involvement in the trial. Random sequence will be generated by a computer permuted blocks of eight, stratified by age (≤ or > 45 years old) and dizziness (yes or no), with allocation ratio 1:1:1:1. Allocation will be concealed in sequentially numbered, sealed, opaque envelopes.

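### Physiotherapist is a randomised factor crossed with all four arms, but the described model leaves it out; adding it is a cheap improvement, not the repair of a bias

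*Protocol article*

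**What the plan says.** The section Physiotherapist training and treatment fidelity states: "The interventions will be provided by five physiotherapists who are experienced in the trial interventions". It adds "Each physiotherapist will deliver all intervention arms", so physiotherapists are crossed with arms rather than nested in them. On who treats whom it says: "The physiotherapists will be randomly assigned to each participant using computerized random numbers". It does not say whether that list is balanced by arm.

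Under Randomization and allocation concealment, allocation to arm uses permuted blocks of eight, "stratified by age (≤ or > 45 years old) and dizziness (yes or no), with allocation ratio 1:1:1:1". Physiotherapist is not a stratum.

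Under Statistical analysis, "Two-way mixed ANOVA will be used to determine within-subject and between subject variables", and "Differences in mean change (baseline minus follow-up) will be compared between groups using baseline values of the outcomes as covariates". No physiotherapist term is named, and no look at the module effects by physiotherapist.

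**The concern.** Who delivers treatment can matter here. There are 12 sessions per participant, mobilisation technique is left to the physiotherapist (Table 3), and programmes are individualised. The trial randomises physiotherapist and crosses it with every arm, so differences between physiotherapists could be removed from the error and the consistency of the module effects could be inspected. The described analysis does neither.

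Two separate things are at stake. The first is precision: between-physiotherapist variance stays in the residual. The second is generality. The Discussion expects the findings to inform practice guidelines, and so physiotherapists other than these five. If the sensorimotor or balance module works better in some hands than in others, the ordinary standard error is too small for that wider inference.

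**Working it through.** The article gives no figure of its own on this point, so there is none to reproduce. Inputs from the documents: five physiotherapists; 42 per arm recruited (168 in total); 35 per arm analysable. Assumed, because the documents give neither: the physiotherapist ICC (0 to 0.20) and the between-physiotherapist SD of a module effect, tau (0.1 to 0.3 outcome SD).

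**1. Chance imbalance, if the list is unrestricted (an assumption).**
- Expected participants per physiotherapist per arm: 42/5 = 8.4. SD = √(42 × 0.2 × 0.8) = 2.6.
- In 20,000 simulated trials, the largest between-arm gap for any one physiotherapist had median 8 (5th to 95th percentile 5 to 11).
- SD of the resulting shift in a main effect (84 v 84): √(5 × 2 × 0.16/84) = 0.138 of the between-physiotherapist SD. At ICC 0.05 this is 0.138 × √0.05 = 0.03 outcome SD, against a standard error of √(4/168) = 0.154.

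**2. Does the unadjusted analysis account for that shift?** Its variance is 0.138² × ICC = 0.019 × ICC. With five equally loaded physiotherapists, about 4/5 of the ICC lands in the residual. That contributes (4/168) × 0.8 × ICC = 0.019 × ICC to the squared standard error. The two agree, so the ordinary standard error already covers the shift. Simulation of a 35 v 35 comparison confirms this: type I error without the term was 5.1% to 5.2% for ICC 0 to 0.20, and bias was within 0.005 SD.

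**3. What the term buys.** Take the 2 × 2 model with 35 per arm (N = 140, 70 v 70) and a main effect of 0.474 SD, for which power is about 80%.
- Cost: residual degrees of freedom fall from 136 to 132. With an unbalanced list the variance rises by about 136/132 = 1.03, so the standard error rises by about 1.5%. The standardised effect falls from 2.80 to 2.76, and power from 80% to about 79%.
- Gain: residual variance falls by a factor of about (1 - ICC). At ICC 0.10, 0.90 × 1.03 = 0.927; 2.80/√0.927 = 2.91; power is about 83%.

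Simulation of the factorial model gives the same picture:

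| Assumed ICC | Change in power from adding the term |
|---|---|
| 0 | about -1 point |
| 0.02 to 0.05 | roughly nil |
| 0.10 | about +3 points |
| 0.20 | about +6 points |

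If assignment is blocked within arm, the cost at ICC 0 essentially disappears.

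**4. Varying module effects, inference beyond these five.** Nominal SE = √(4/168) = 0.154. True SE = √(4/168 + tau²/5).

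| tau (outcome SD) | True SE | Ratio to nominal | Actual error at nominal 5% |
|---|---|---|---|
| 0.1 | 0.161 | 1.04 | 6% |
| 0.2 | 0.178 | 1.16 | 9% |
| 0.3 | 0.204 | 1.33 | 14% |

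The last column is 2Φ(-1.96/ratio). With N = 140 the ratio at tau 0.2 is √(0.0286 + 0.008)/√0.0286 = 1.13.

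A main-effect term does not cure this. In simulation with 35 per arm at tau 0.2, error was 8.6% and 9.0% for the models without and with the term, which is no material difference.

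**The case against.** The case against is substantial, and most of it stands.

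- A reader might infer that assignment is unrestricted. The text says only that computerised random numbers are used, in contrast to the blocks and strata it names for arm. The counts in step 1 are therefore conditional on an assumption.
- A reader might infer that uneven caseloads bias the arm comparison. They do not: physiotherapist is random with respect to arm, and step 2 shows the error term already covers the chance shift. Crossing and random assignment are themselves protective features.
- A reader might infer that delivery rests on personal judgement after one short training session. In fact progression follows achievement of the current level's target, with targets set out in Table 4. Free choice of technique concerns mobilisation, which all arms receive. Experience requirements, a manual and case-note monitoring also apply, and "Treatment sessions will be audited to ensure that the physiotherapists are managing patients as per the trial treatment protocols". These limit drift, but they do not estimate physiotherapist differences or remove them from the error.
- The plan is powered "to detect a significant difference of 21.9 cm^2^ (SD = 12.3) for postural sway and 4.5° (SD = 3.2) for JPE", that is 21.9/12.3 = 1.78 and 4.5/3.2 = 1.41 SD. At those sizes, 35 v 35 has power above 99.9%, so the gain in step 3 matters only if true effects are much smaller.
- An analysis plan that is not shown may contain a physiotherapist term. That is possible, so its absence from a condensed article is weak evidence. The article does, however, name its covariate, and physiotherapist is not mentioned.
- Five physiotherapists with about 8 participants per cell estimate tau poorly. That is true, and it limits what the sensitivity analysis can show.

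**Conclusion.** The point holds as a modest improvement. The described analysis does not use a factor that the trial randomises and crosses with every arm. Nothing in the article is contradictory on this, and no primary conclusion is invalidated: there is no bias and type I error stays near 5% when the module effects do not vary between physiotherapists.

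The gain from the term depends on an ICC that the documents do not give. It ranges from a loss of about 1 point of power to a gain of about 6.

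The interaction concern is distinct. It rests on an assumed tau, applies only to inference beyond these five physiotherapists, and is not addressed by the main-effect term. Only a report of effects by physiotherapist bears on it, and imprecisely.

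**What to change.** 1. Add physiotherapist as assigned (five levels, 4 degrees of freedom) to the primary factorial model, and record this before outcome data are compared by arm.
2. State whether the physiotherapist list is balanced by arm. If it is not, assign physiotherapists to remaining participants in permuted blocks of five within arm, so that a fully blocked arm of 42 would give each physiotherapist 8 or 9. Participants already enrolled keep their assignment; the model term handles any earlier imbalance.
3. As a sensitivity analysis, report the sensorimotor and balance effects by physiotherapist, with the estimated variation and its uncertainty. Say plainly that five physiotherapists estimate it imprecisely and that the main-effect term does not correct for it.

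Cost: up to 4 degrees of freedom, a revised list and slightly less flexible scheduling. No extra participants, visits or staff are needed, and treatment content is unchanged.
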